### Design

The trial will include about 360 chronically depressed outpatients. About 180 patients will have a clear preference foreither PAT or CBT. After baseline assessment (t0) they will be assigned to a study therapist offering the preferred intervention. About 180 patients will come without preference and accept to be randomized to either PAT or CBT. Randomization will take place after baseline assessment (t0). Figure1 summarizes the 2 (preference) by 2 (psychotherapies) by 4 (time) factorial design.

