**Methods/design:**

Patients are assigned to treatment according to their preference or randomized (if they have no clear preference). Up to 80 sessions of psychodynamic or psychoanalytically oriented treatments (PAT) or up to 60 sessions of CBT are offered during the first year in the study. After the first year, PAT can be continued according to the ‘naturalistic’ usual method of treating such patients within the system of German health care (normally from 240 up to 300 sessions over two to three years). CBT therapists may extend their treatment up to 80 sessions, but focus mainly maintenance and relapse prevention. We plan to recruit a total of 240 patients (60 per arm). A total of 11 assessments are conducted throughout treatment and up to three years after initiation of treatment. The primary outcome measures are the Quick Inventory of Depressive Symptoms (QIDS, independent clinician rating) and the Beck Depression Inventory (BDI) after the first year.

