### Sample size calculation

Sample size calculation was based on meta-analyses with similar interventions in similar patient groups using similar outcome instruments [10,11,34,35]. Based on the Hamilton Depression Rating Scale (a 17-item clinician rating form, similar to the QIDS-C) we expect pre-post effect sizes for psychotherapies of depression of *d* = 1.2. A study including a direct comparison of PAT and CBT is not available. Therefore, we used meta-analysis of comparing psychotherapy with psychiatric therapy with depressed out-patients to extrapolate a probable effect size of *d* = 0.50 between treatments of different efficacy at post-treatment. To detect this difference at *α* = 0.025 (two-tailed) with a power of 0.80, a minimum number of 60 patients per cell are required (see Figure1).

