### Secondary analyses

Self-report questionnaires and observer ratings will be analyzed by mixed models with repeated measurements. With two co-primary outcomes, we will conduct the tests at a 0.025 level of significance (two-tailed) to adjust for the multiple comparison issue. Further analyses will include cross-sectional analyses to compare therapists; subgroup analyses of subjects’ and therapists’ conditions; and costs of the SP treatment.

Descriptive statistics showing the measurements over time will be presented whenever appropriate. Serious adverse events and cases of drop-outs will be analyzed descriptively.

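### The Abstract plans 240 patients and the Design section about 360; nothing in the text links the two, and per-cell power is about 68% or 86% depending on which is meant

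*Protocol article*

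**What the plan says.** The protocol article gives the planned size in three places.

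- **Abstract, Methods/design:** "We plan to recruit a total of 240 patients (60 per arm").
- **Methods, Design:** "The trial will include about 360 chronically depressed outpatients". This is broken down as "About 180 patients will have a clear preference foreither PAT or CBT" and "About 180 patients will come without preference and accept to be randomized to either PAT or CBT". The first group goes to a study therapist after baseline; the second is randomised after baseline. The same section describes a factorial design with two assignment modes and two psychotherapies, hence four cells.
- **Methods, Sample size calculation:** the assumed difference is d = "0.50 between treatments of different efficacy at post-treatment", and the requirement is set at alpha = "0.025 (two-tailed) with a power of 0.80, a minimum number of 60 patients per cell are required".

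The section headed Secondary analyses explains the alpha: two co-primary outcomes, each tested at two-sided 0.025. The Trial status section says that recruitment is still under way.

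**The concern.** The Abstract and the Design section give different totals for what reads as the same quantity. They differ by 120 patients, or 50% of the smaller figure, which is more than the word 'about' can cover.

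The total determines how many patients enter the randomised stratum, and only that stratum gives a randomised comparison of PAT with CBT. On one total, that comparison falls short of the 80% power that the protocol claims. On the other, it exceeds 80% before any loss to follow-up. A reader cannot tell which trial is being run or what power it has.

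**Working it through.** **Step 1: the totals.**
- Abstract: 60 × 4 cells = 240.
- Sample size calculation: minimum 60 per cell × 4 cells = 240, in agreement with the Abstract.
- Design: 180 + 180 = 360, an average of 360/4 = 90 per cell.
- Gap: 360 − 240 = 120, and 120/240 = 50%.

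The 90 per cell is derived, not stated. In the randomised stratum it assumes 1:1 allocation. In the preference stratum it assumes that patients' choices split evenly, which they need not do. The conflict between 240 and 360 needs neither assumption.

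**Step 2: can attrition link them?** Going from 90 enrolled to 60 analysed needs a loss of 1 − 60/90 = 33.3%. The text gives no attrition rate and no inflation step.

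**Step 3: the protocol's own 60 per cell.** Inputs from the Sample size calculation: d = 0.50, alpha 0.025 two-sided, power 0.80. For two equal groups, by the normal approximation:

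n per cell = 2 (z for 0.9875 + z for 0.80)² / d² = 2 (2.241 + 0.842)² / 0.25 ≈ 76.04, so 77. The noncentral t gives 78.

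The 60 is not reproduced under nearby settings either:

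| Alpha | n per cell, normal approximation |
|---|---|
| 0.025 two-sided | 77 (t-test: 78) |
| 0.05 two-sided | 63 (t-test: 64) |
| 0.025 one-sided | 63 |
| 0.05 one-sided | 50 |

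**Step 4: power at each total**, d = 0.50, two-sided alpha 0.025, unadjusted comparison of two equal groups. Normal approximation: power = Φ(d√(n/2) − 2.241).

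- n = 60: 0.5 × √30 = 2.739; Φ(0.497) = 69.0%. With the t distribution, 68.0%.
- n = 90: 0.5 × √45 = 3.354; Φ(1.113) = 86.7%. With the t distribution, 86.2%.

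The smallest d detectable with 80% power, 3.083 × √(2/n), is 0.56 at 60 per cell and 0.46 at 90 per cell.

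**Step 5: sensitivity to loss from 90 per cell.** These rates are illustrations; none is in the protocol.

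| Assumed loss | Analysed per cell | Power (t-test) |
|---|---|---|
| none | 90 | 86% |
| 20% | 72 | 77% |
| one third | 60 | 68% |

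Keeping 78 of 90 (a loss of 12/90 = 13%) would just preserve 80%.

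**Step 6: treatment effect pooled over assignment.** Each treatment would then have 120 patients (N = 240) or 180 (N = 360), with t-test power of 94.6% or 99.4%. This comparison includes patients who chose their treatment.

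**The case against.** The strongest defence is that both figures belong to one plan. The sample size section speaks of a minimum, the Design section says 'about', and 90 less one third is exactly 60. On that reading 360 are enrolled and 240 are analysed, there are not two competing powers, and the only slip is the Abstract's verb. Figure 1, captioned as showing projected numbers and cited in both the Design and Sample size sections, could contain that flow. It was not available for this review, and its absence is not a fault of the plan. The reading is possible but cannot be confirmed. The Abstract says 240 are to be recruited, and the two sentences conflict whatever the figure shows. Treating the 360 as a screening number fails too, because those patients are assigned or randomised.

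A second defence concerns the power contrast. The Statistical analysis section plans covariate-adjusted repeated-measures models with treatment and assignment as factors, not a two-cell t-test. Adjustment could raise power: for 60 per cell to give 80%, 1 − r² must equal 60/77 = 0.779, a baseline correlation of about 0.47. A pooled treatment effect would be well powered at either total. Both points stand, so the 68% and 86% apply only to the per-cell basis that the sample size section itself uses. That section gives no baseline correlation and does not mention pooling.

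Two stronger readings are not supported. A reader might infer that the sample size section backs neither total. In fact 60 × 4 = 240 matches the Abstract; that 60 does not follow from its inputs is a separate matter. A reader might also infer that two targets let recruitment be stopped or extended in the light of results. The protocol describes no interim efficacy analysis, and it places data monitoring, randomisation and evaluation at an independent site.

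**Conclusion.** The inconsistency is real: 240 in the Abstract, in agreement with 60 per cell in the sample size section, against about 360 in the Design section. No available text reconciles them. The planned size is a figure the trial relies on, so this should be corrected.

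On the protocol's per-cell basis the choice moves power for randomised PAT against CBT by about 18 percentage points (86.2 − 68.0), on either side of the stated 80%. This rests on the protocol's d and alpha, an unadjusted t-test, 1:1 allocation and no loss beyond the numbers given. Two qualifications remain: Figure 1 may explain the link, and for a treatment effect pooled over assignment the choice of total matters little.

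**What to change.** 1. State one enrolment target and one evaluable target per cell, linked by an explicit attrition assumption. If 360 enrolled and 240 evaluable is what is meant, say so, give the one-third loss, and correct the Abstract's wording.
2. Fix the size of the randomised stratum in its own right, with its allocation ratio.
3. Restate the power that the chosen evaluable number delivers at two-sided alpha 0.025. If 80% is kept on an unadjusted two-cell basis, about 78 evaluable per cell are needed (156 in the randomised stratum, 312 over four equal cells). If the calculation relies on baseline adjustment or pooling over assignment, state that and the correlation assumed.
4. Use the same figures in the Abstract, Design and Sample size calculation sections, and check that Figure 1 agrees.

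The cost is wording and a short recalculation if the chosen target is the one already budgeted. A larger target would cost the additional recruitment, treatment and follow-up.

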**Figure 1 F1:**
[figure not shown]
Study design (projected numbers).

### Outcome

The primary outcome measures are the Quick Inventory of Depressive Symptoms (QIDS [26]) (independent clinician rating) and the Beck Depression Inventory (BDI-2) one year after initiation of treatment (t4). Treatment response is defined as a decline of at least 50% from t0 (baseline, pre-treatment) to t4 (12 months after intake. Remission is defined by a QIDS-score below 6. A relapse is defined when the criteria of a major depressive disorder (MDD) are fulfilled, for example, a QIDS-score above 9 is documented or hospitalization or outpatient treatment are needed.

Secondary outcome measures include the Beck Depression Inventory (BDI 2 [27]), the QIDS-self-rating, the Symptom-Checklist (SCL-90R [28]), the Depressive Experience Questionnaire (DEQ [29]) and the Dysfunctional Attitude Scale (DAS [30]). Furthermore, we assess social functioning (SOFAS [31]), the Helping Alliance Questionnaire (HAQ [32], and recurrence of depressive episodes assessed by the longitudinal follow-up evaluation interview (LIFE [33]).

### Sample size calculation

Sample size calculation was based on meta-analyses with similar interventions in similar patient groups using similar outcome instruments [10,11,34,35]. Based on the Hamilton Depression Rating Scale (a 17-item clinician rating form, similar to the QIDS-C) we expect pre-post effect sizes for psychotherapies of depression of *d* = 1.2. A study including a direct comparison of PAT and CBT is not available. Therefore, we used meta-analysis of comparing psychotherapy with psychiatric therapy with depressed out-patients to extrapolate a probable effect size of *d* = 0.50 between treatments of different efficacy at post-treatment. To detect this difference at *α* = 0.025 (two-tailed) with a power of 0.80, a minimum number of 60 patients per cell are required (see Figure1).

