### Randomization

As Figure1 shows, in a partial randomization preference trial, patients are asked if they have a preference for one specific treatment (PAT or CBT). Treatments are outlined to them in terms of a general description (see box for the instructions). If they articulate a specific preference, they are assigned accordingly (preference arm). If they articulate no specific preference, they are randomized (randomization arm).

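### The 0.80 power claim needs at least 60 patients in every cell, but patients' choices decide the cell sizes, so the planned enrolment does not secure them

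*Protocol article*

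**What the plan says.** The Sample size calculation section takes a between-treatment effect from related meta-analyses ("extrapolate a probable effect size of *d* = 0.50 between treatments of different efficacy at post-treatment"), sets the test level ("To detect this difference at *α* = 0.025 (two-tailed") and concludes "with a power of 0.80, a minimum number of 60 patients per cell are required". It refers to Figure 1 for the cells. The Design section describes them as two assignment modes by two therapies, so there are four.

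The Randomization section fixes how patients reach a cell: "If they articulate a specific preference, they are assigned accordingly (preference arm"). Those without a specific preference are randomised.

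Enrolment is given in two places. The abstract says "We plan to recruit a total of 240 patients (60 per arm"). The Design section says "The trial will include about 360 chronically depressed outpatients", and divides them by stratum: "About 180 patients will have a clear preference foreither PAT or CBT" and "About 180 patients will come without preference and accept to be randomized to either PAT or CBT". It gives no number per therapy within either stratum. Figure 1 is captioned as showing projected numbers but is not in the text at hand.

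**The concern.** The sample size statement treats four cells as if the trial could fill each to a set number. Under the allocation rule it controls only one division, the one between PAT and CBT among randomised patients. The other two follow from what patients want: the share who are randomised, and the PAT:CBT split among those with a preference. The Patient preferences section of the Background itself notes that patients with strong preferences may refuse randomisation.

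At stake is mainly the randomised PAT-CBT comparison, the only one of the two therapies that is free of self-selection. It shrinks each time one more patient states a preference. The enrolment total could be reached with clearly less power for that comparison than the stated 0.80, and the power statement would not show it. Hypothesis B (preferred against randomised therapy) and the planned test of whether treatment differences depend on assignment also rely on the individual cells.

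**Working it through.** **Inputs from the document.** d = 0.50; two-sided alpha 0.025; target power 0.80; minimum 60 per cell; four cells; totals of 240 (60 per arm) and about 360 (about 180 per stratum).

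**Assumptions, because the document gives no figures.** 1:1 randomisation; no drop-out; the randomised shares and preference splits below; equal strata of 120 at the total of 240, except where the share is varied.

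**Formula.** Two-sample t-test with cells a and b: noncentrality = d × √(ab/(a+b)), with a+b−2 degrees of freedom. Power comes from the noncentral t distribution at two-sided alpha 0.025.

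**The plan's own figure first.** At 60:60 the noncentrality is 0.50 × √(3600/120) = 2.739 and power is 0.680. The stated inputs need 77.3 per cell, so 78, for power of 0.80. The figure of 60 thus does not reproduce even with perfect balance. That is a separate matter; what counts here is the change in power as the cells move away from balance.

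**Randomised pair** (cell size = total × randomised share / 2):

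| Total | Randomised share | Per cell | Power |
|---|---|---|---|
| 240 | 50% | 60 | 0.680 |
| 240 | 40% | 48 | 0.570 |
| 240 | 30% | 36 | 0.437 |
| 360 | 50% | 90 | 0.862 |
| 360 | 40% | 72 | 0.768 |
| 360 | 30% | 54 | 0.628 |

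**Preference pair:**

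| Stratum | Split | Cells | Power |
|---|---|---|---|
| 120 | 50:50 | 60:60 | 0.680 |
| 120 | 70:30 | 84:36 | 0.596 |
| 120 | 80:20 | 96:24 | 0.471 |
| 180 | 50:50 | 90:90 | 0.862 |
| 180 | 2:1 | 120:60 | 0.816 |
| 180 | 70:30 | 126:54 | 0.791 |
| 180 | 80:20 | 144:36 | 0.664 |

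**When is the minimum of 60 met?**

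- *Total 240.* 240/4 = 60, so the minimum equals the average and any imbalance puts some cell below it. Even if preferences are truly 50:50, the chance that 120 preference patients divide exactly 60:60 is C(120,60)/2^120 = 0.07.
- *Total 360, randomised pair.* The two cells need 120 patients, so a randomised share of at least 120/360, one third.
- *Total 360, preference pair.* With 180 in the stratum, both cells hold 60 up to a split of 120:60, or 2:1. The chance that both reach 60 is 0.97 if 60% truly prefer one therapy, 0.71 at 65% and 0.18 at 70%.

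**Pooled contrast, for comparison.** PAT against CBT over both strata at a total of 240: 120:120 gives 0.946. A randomised 60:60 plus a preference split of 96:24 gives 156:84 and 0.924.

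**The case against.** Four arguments stand against the point.

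- *The plan does contain targets below the total.* The abstract says 60 per arm, the Design section gives about 180 per stratum, and Figure 1 carries projected numbers. This stands: it would be wrong to infer that recruitment is planned only as totals. But a projection does not fill a cell when patients choose the cell.
- *At about 360 there is room.* This also stands. A 60:40 mix of preference and randomised patients still leaves 72 per randomised cell. A 2:1 preference split keeps 60 in the smaller cell with power of about 0.82, and even 126:54 gives 0.79, close to the stated 0.80. So a reader may not conclude that the planned enrolment will fail to deliver the cells, only that it does not secure them.
- *The powered contrast is not named.* If d = 0.50 refers to PAT against CBT pooled over assignment, an uneven choice costs little. That stands as arithmetic. However, the section states its requirement per cell and not per therapy, and the pooled contrast mixes self-selected with randomised patients.
- *Quotas or recruitment caps may be in the full protocol.* They may, and their absence from an article is not the point made here. The point is that the article states a power that depends on cell sizes, beside an allocation rule that leaves those sizes to patients.

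**Conclusion.** The point holds in a limited form: the power of 0.80 is tied to a minimum in every cell that the stated allocation rule does not secure. How much this matters depends on which total applies.

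At 240 the claim has no tolerance. Moving from 50% to 40% randomised lowers power for the randomised comparison from 0.68 to 0.57, and a 70:30 preference split lowers the preference comparison from 0.68 to 0.60. At about 360 moderate imbalance is absorbed. There the minimum fails only with marked imbalance, for example 30% randomised (54 per cell, power 0.63) or 70:30 in the preference stratum (54 in the smaller cell, power 0.79).

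Two stronger readings are not supported. The documents do not show that the trial will be underpowered, because every share used here is an assumption. And the 0.68 at 60 per cell cannot be blamed on patient choice, since it arises with perfectly equal cells. All figures assume no drop-out, and drop-out would lower them.

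**What to change.** In Design and Sample size calculation:

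1. Say that the power claim refers to the randomised PAT-CBT comparison.
2. State the recruitment target as a number per randomised cell, and report the power at the number expected there. With the stated inputs that is 0.68 at 60, 0.77 at 72 and 0.86 at 90, before drop-out.
3. For the preference stratum, replace the equal-cell power statement with power or precision over a range of splits, for example 50:50 to 80:20.

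Closing a preference cell once it is full is not recommended as part of this change. It would turn away patients who refuse randomisation, and the article says the preference arm exists so that they can be included.

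The cost is a few sentences and a small table, and the planned total need not change. The downside is that the stated power for some comparisons will look less favourable than 0.80. The article reports recruitment as ongoing, so the statement can still be corrected before the data are analysed.

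### At the stated inputs, 60 patients per cell give about 68% power for d = 0.50, not 80%; 77 to 78 per cell are needed before any drop-out

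*Protocol article*

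**What the plan says.** The Sample size calculation section of the protocol article gives all its inputs together. The assumed effect is a standardised difference of "0.50 between treatments of different efficacy at post-treatment", the level and power are "0.025 (two-tailed) with a power of 0.80", and the conclusion is that "with a power of 0.80, a minimum number of 60 patients per cell are required".

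The test level is not a slip. The Secondary analyses section gives the reason for it: with two co-primary outcomes, "we will conduct the tests at a 0.025 level of significance (two-tailed) to adjust for the multiple comparison issue".

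The abstract carries the 60 into the recruitment target: "We plan to recruit a total of 240 patients (60 per arm"). The Design section gives another total: "The trial will include about 360 chronically depressed outpatients", about 180 of them with a preference and about 180 randomised. The sample size section mentions neither a drop-out allowance nor a gain from baseline adjustment.

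**The concern.** A difference of half a standard deviation at two-sided 0.05 and 80% power is known to need a little over 60 patients per group. Halving alpha to 0.025 must raise that number, so 60 at the stricter level cannot be right for an unadjusted comparison.

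This is the only power statement in the article. It is made per cell, and the PAT versus CBT comparison that randomisation protects is one cell against another. If that comparison has less power than stated, a non-significant result says less about similarity of the two therapies than a reader who trusts the 80% would suppose. Attrition adds to this: the article itself hypothesises different drop-out in preferred and randomised therapy.

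**Working it through.** **Inputs**
- d = 0.50, so the standard deviation is 1 (Sample size calculation)
- alpha = 0.025 two-sided (Sample size calculation; confirmed in Secondary analyses)
- power = 0.80 (Sample size calculation)
- n = 60 per cell (Sample size calculation; abstract)

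**1. Sample size at the stated inputs.** For two equal groups, n = 2 × [(z₁₋α/₂ + z₁₋β) / d]².

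n = 2 × [(2.2414 + 0.8416) / 0.50]² = 76.04, so 77 per cell. The t-test (noncentral t) needs 78, where power is 0.804. The plan's 60 is not reproduced. The gap is 17 to 18 patients per cell; four cells of 78 make 312 patients against 240.

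**2. Power at 60 per cell.** Power = Φ(d / √(2/n) − z₁₋α/₂) = Φ(0.50 / √(2/60) − 2.2414) = Φ(2.7386 − 2.2414) = Φ(0.497) = 0.690. The t-test gives 0.680. The difference detectable with 80% power by t-test at 60 per cell is d = 0.57.

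**3. Other readings of the test level**

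| Level | n per cell, normal / t | Power at 60, normal / t |
|---|---|---|
| 0.025 two-sided (as stated) | 77 / 78 | 0.690 / 0.680 |
| 0.05 two-sided, or 0.025 one-sided | 63 / 64 | 0.782 / 0.775 |
| 0.05 one-sided | 50 / 51 | 0.863 / 0.859 |
| 0.0125 two-sided | 90 / 91 | 0.595 / 0.581 |

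None returns 60. The nearest is 0.05 two-sided, which suggests that the split of alpha was not carried into n. That is inference, and the result does not depend on it.

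**4. Baseline adjustment.** Analysis of covariance multiplies the variance by 1 − r², where r is the baseline-to-12-month correlation. Setting 76.04 × (1 − r²) = 60 gives r = 0.46; the t-test version needs about 0.48. At r = 0.50, power by t-test is 0.81 with 60 per cell and 0.71 with 48. The article gives no value of r.

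**5. Loss to follow-up (rates assumed; t-test, unadjusted)**

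| Loss | From 60 per cell | Power | From 90 per cell | Power |
|---|---|---|---|---|
| none | 60 | 0.68 | 90 | 0.86 |
| 10% | 54 | 0.63 | 81 | 0.82 |
| 20% | 48 | 0.57 | 72 | 0.77 |
| 30% | 42 | 0.51 | 63 | 0.70 |

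The 90 is the Design section's 360 divided evenly over four cells; the even split is an assumption.

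**The case against.** The case on the other side accepts that 60 does not reproduce and disputes the consequences.

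- **The trial may be larger than 240.** The Design section's 360 would give about 90 per cell and power of 0.86. The word minimum in the sample size section could mean that the surplus over 60 is an attrition margin. This is fair: power is 0.68 or 0.86 depending on which total applies. But the article does not link the 360 to the calculation, the abstract contradicts it, and it does not make 60 the required number.
- **Baseline adjustment is planned.** The Statistical analysis section makes intake symptoms a covariate, and a correlation just under 0.5 would bring 60 per cell to 80% power. This also stands as a limit: 0.68 is the power of the unadjusted comparison the paragraph describes, not a proven figure for the planned model. The paragraph neither invokes adjustment nor states a correlation.
- **The treatment effect may be tested over all four cells.** At 120 against 120, power is about 0.95. The calculation, however, is expressed per cell, and pooling adds patients who chose their own treatment.
- **Success on either co-primary outcome may suffice.** If d = 0.50 holds on both, the chance of at least one significant result at 60 per cell is 0.84, 0.80 or 0.75 for assumed outcome correlations of 0.5, 0.7 and 0.9 (normal approximation). The article states no such rule, so the one-in-three miss rate must be read as per outcome.
- **A condensed article may leave attrition to the full protocol.** Accepted. Attrition is supporting material here, and the figures that matter are those up to the 12-month primary assessment.

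**Conclusion.** The concern holds. From the article's own inputs, 77 to 78 evaluable patients per cell are required, and 60 per cell give 68 to 69% power, 11 to 12 percentage points below the stated 80%. The risk of missing a true d = 0.50 is about 32%, against the 20% implied.

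This risk is for one outcome and one unadjusted comparison of two cells of 60, with complete data. It would be smaller with about 90 per cell or with a strong baseline covariate, and larger with drop-out. None of these conditions makes the sentence correct as written. As it is the sole justification of the sample size for the co-primary outcomes, it must be corrected.

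**What to change.** Rewrite the sample size paragraph in one of these forms:

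1. About 77 to 78 evaluable patients per cell are needed for d = 0.50 at two-sided 0.025 with 80% power.
2. With 60 per cell, power for d = 0.50 is about 68%, and the difference detectable with 80% power is d = 0.57.
3. With baseline adjustment, 60 per cell suffice under a stated baseline-to-12-month correlation (just under 0.5 if nobody is lost), with the source of that value.

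In each case, name the comparison the calculation refers to, give power over a range of attrition up to 12 months (for example 10 to 30%), and say whether 240 or about 360 patients is the target, so that the abstract and the Design section agree.

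The cost is the wording of one paragraph, the reconciled total, and a less favourable stated figure. The test level, outcomes and analysis stay as they are.
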